### Inclusion Criteria

This study included systemically healthy patients who (1) were nonsmokers, (2) were aged between 18 and 65 years, (3) had teeth presenting Miller class I or II areas with multiple GRs on the buccal or labial surfaces present in either the maxilla or mandible, (4) had a GR depth of ≥2 mm, and (5) had X-rays of adequate interdental bone (separation across crestal bone and CEJ ≤ 2 mm).

### Exclusion Criteria

The following patients were excluded: patients using tobacco products, uncooperative patients, individuals with inadequate oral hygiene and a plaque score ≥1 after nonsurgical treatment, individuals with a history of periodontal surgical treatment in the selected research area, pregnant or lactating women, patients with mobile or severely decayed teeth, and those with irregularly placed teeth. Additionally, patients with systemic conditions such as hematological disorders (eg, anemia, thrombocytopenia, or clotting factor deficiencies), those undergoing anticoagulant therapy, or individuals with chronic kidney disease, uncontrolled diabetes mellitus, liver diseases (eg, cirrhosis), and severe cardiovascular conditions requiring anticoagulant therapy were excluded to ensure the study’s integrity and minimize complications.

### Procedure

The process of scaling, root planing, and polishing will be done on every patient. The patient will be instructed to use the modified Stillman brushing method to minimize brush injury. Unless the patients receive a plaque score ≤1, oral hygiene instructions will be provided. A review will be conducted 6 weeks later to evaluate plaque control and tissue response. The patient’s participation in the study is contingent on their poor oral hygiene. The patient will provide with informed consent after being given information about the study plan.

### Clinical Measurements

#### Indices

All patients’ oral hygiene and gingival status are reviewed on the day of surgery, 3 and 6 months apart.

Plaque index (PI) [17]: The presence of plaque is evaluated on the labial or buccal and lingual surfaces of all teeth after the application of the disclosing agent (Table 1). The PI value for the tooth is calculated by splitting all the points around it by 2. The PI score for each individual person is gained by summing the PI scores of all teeth and dividing by the number of teeth inspected.

Papillary bleeding index [18]: The exact mesial introduction of a periodontal probe (William’s Calibrated Probe) into the gingival sulcus at the papilla’s apex will be followed by a coronal advancement to the tip of the papilla. On the same papilla, this is repeated on the distal side. On a scale of 0-4, the degree of potential bleeding is evaluated. The papillary bleeding index score per individual will be calculated by adding up all papillary bleeding index scores to the number of surfaces analyzed.

**Table 1 table1:** Plaque index.

Score	Criteria
0	Absence of plaque.
1	Distinct plaque deposits on the cervical surface of a tooth.
2	Thin, uninterrupted layer of plaque (up to 1 mm) covering the tooth’s cervical margin.
3	Plaque band broader than 1 mm but covering less than one-third of the crown.
4	Plaque covering not less than one-third but less than two-thirds of the crown.
5	Plaque that covers two-thirds or more of the crown.

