**Objective:**

The objective of this study is to compare the effectiveness of T-PRF and CTGs from the tuberosity area in managing gingival recession defects using the M-VISTA technique. The study aims to evaluate improvements in clinical outcomes, including pocket probing depth (PPD), clinical attachment level (CAL), relative gingival margin level (RGML), recession depth (RD), and width of keratinized gingiva (WKG), as well as plaque and bleeding indices.

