**Methods:**

The proposed methodology entails conducting a randomized clinical trial over 2 years with 24 participants, each presenting with multiple gingival recessions (>2 mm, Miller’s Class I or II) on the buccal or labial aspects of teeth in the maxilla or mandible. Participants will be randomly allocated into 2 groups: the test group and the control group. The M-VISTA technique will be used for root coverage using T-PRF in the test group and tuberosity CTG in the control group as regenerative materials. Their effectiveness will be compared by evaluating PPD, CAL, RGML, RD, and WKG. Additionally, the plaque index will be calculated by dividing the total plaque index score of all teeth by the number of teeth examined, and the papillary bleeding index will be assessed using a periodontal probe with scores evaluated on a scale of 0-4 based on bleeding potential. Data will be analyzed using Student paired and unpaired t tests to compare results from baseline to 3 and 6 months for each group.

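### The per-person papillary bleeding index is worded as the scores added to the number of surfaces, where a division is evidently meant (minor, wrong as written)

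*Protocol article*

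**What the plan says.** The Objective in the abstract of the protocol article lists several clinical measurements to be compared and closes the list with "as well as plaque and bleeding indices". The Indices section schedules both indices for the day of surgery and for 3 and 6 months.

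For the papillary bleeding index, the Indices section describes probing the mesial and distal side of each papilla. It then grades the finding: "On a scale of 0-4, the degree of potential bleeding is evaluated". The per-person score is "calculated by adding up all papillary bleeding index scores to the number of surfaces analyzed". The Methods paragraph of the abstract gives the grading only ("scores evaluated on a scale of 0-4 based on bleeding potential") and no rule for combining sites. No other section gives such a rule for this index.

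For the plaque index, the same Indices section obtains the per-person score by "summing the PI scores of all teeth and dividing by the number of teeth inspected", and the abstract repeats that division.

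**The concern.** Two per-person indices are defined side by side from the same ingredients, a total of scores and a count of units examined. One rule divides the total by the count. The other, as worded, adds the count to the total. A total plus a count is not an average. It does not start at zero when there is no bleeding, and it grows with the number of surfaces examined even when bleeding is the same.

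The Statistical Analysis section plans paired t tests for change from baseline and unpaired t tests between groups. It does not list the variables, but the bleeding index is one of the measures named in the Objective, so those tests presumably apply to it. At stake is whether its values can be interpreted, and whether differences in surface count between patients enter a comparison that is meant to reflect bleeding only.

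**Working it through.** **Inputs from the protocol article**
- Site score x_i, from 0 to 4 (Indices; abstract, Methods).
- Per-person rule: the scores added to the count of surfaces (Indices).
- Number of surfaces n: not stated for this index.
- Group size: 12 per arm (Sample Size Calculation).

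The article gives no per-person bleeding score or range, so there is no figure of its own to reproduce.

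**Three readings of the rule**, with m the mean site score:

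| Reading | Formula | Range | No bleeding |
|---|---|---|---|
| Literal | sum(x_i) + n = n(m + 1) | n to 5n | n |
| Sum only | sum(x_i) = n·m | 0 to 4n | 0 |
| Division | sum(x_i) / n = m | 0 to 4 | 0 |

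Only division gives a value that does not depend on n at equal bleeding.

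**Illustration with assumed counts.** Assume papillae lie only between adjacent teeth within each of two unbroken arches, with two sides per papilla. Then n = 2 × (teeth − 2).
- 28 teeth: n = 2 × 26 = 52.
- 20 teeth: n = 2 × 18 = 36.

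| Mean site score | Literal, n = 52 | Literal, n = 36 | Divided, either n |
|---|---|---|---|
| 0 | 52 | 36 | 0 |
| 0.5 | 26 + 52 = 78 | 18 + 36 = 54 | 0.5 |
| 1 | 52 + 52 = 104 | 36 + 36 = 72 | 1 |

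At the same mean of 0.5 the literal scores differ by 78 − 54 = 24. A patient with 52 surfaces and no bleeding (52) scores almost the same as one with 36 surfaces and a mean of 0.5 (54).

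**Effect on the planned tests**
- *n equal for all patients and visits.* The literal score n(m + 1) is a linear function of m with the same constants for everyone. Group differences and standard errors are both multiplied by n, and the added n cancels in any difference. Paired and unpaired t statistics are therefore the same as for m.
- *n differs between patients but is constant within each.* In the paired change the added n cancels, leaving n × (change in m), so patients with more surfaces weigh more. In the unpaired comparison, n enters both as a multiplier and as an added term.
- *Chance imbalance in n.* Suppose every patient has mean bleeding 0.5 and the arms average 50 and 46 surfaces. The literal means are 50 × 1.5 = 75 and 46 × 1.5 = 69, a difference of 6 where the difference in mean bleeding is 0. These counts are assumed; they show the mechanism, not an expected size.

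**The case against.** The strongest reply is that this is garbled wording and not a decision to add a count. A count of surfaces has no evident use here except as a denominator, the plaque rule beside it shows the intended form, and the article uses loose synonyms for technical terms elsewhere. The index is also a cited instrument, so staff may score it from the source. This largely stands: a slip is the likeliest explanation, and a reader should not infer that the trial will in fact compute, or has computed, sum plus n. Nothing in the article shows that. The sentence is still the only stated rule for combining sites, and it names the wrong operation, so this is a misstatement and not a detail left to another document.

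Three stronger readings are tempting, and the article does not support them.
- *The score contradicts the trial's own 0-4 scale.* That scale is given for the degree of bleeding at the examined site. No range is stated for the per-person score, so a total outside 0 to 4 is not in itself a contradiction.
- *The rule biases the comparison of treatments.* Allocation is random, so surface counts are not expected to differ systematically between arms. Varying counts bring noise and the possibility of chance imbalance with 12 per arm.
- *A main result is at risk.* The bleeding index comes last in the Objective. It is absent from the aims at the end of the Introduction, from the list of outcome measurements under Clinical parameters, and from the expected Results. The sample size section does not name it either.

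**Conclusion.** The rule is wrong as written, and the point is minor. The literal per-person score is n(m + 1): it equals n when there is no bleeding, and it differs between patients with equal mean bleeding whenever their surface counts differ. That algebra needs no assumption beyond reading the sentence literally.

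The sizes do rest on assumptions. The counts of 52 and 36 surfaces, and the scores of 78 and 54 at a mean of 0.5, are illustrative because the article gives no surface count. If the number of surfaces varies between patients, the consequence is added noise and possible chance imbalance in one peripheral index. If it is constant, the t tests are unaffected and only the meaning of the reported values suffers. The design, the sample size and the other outcomes are untouched.

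**What to change.** Replace the sentence with a rule parallel to the plaque index: the per-person papillary bleeding index is the sum of all papillary scores divided by the number of surfaces (papilla sides) analyzed. This gives a mean on the 0-4 site scale. Derive the scores for the day of surgery, 3 months and 6 months from the recorded site scores by that one rule.

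The cost is one sentence of text. If division is already what is done, nothing else changes. If any per-person score was derived another way, it can be recalculated from the site scores, provided these were kept, before the final analysis scheduled for June to July 2026. No new measurement and no change to design or test is needed.

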#### Clinical parameters

Clinical parameters measured for outcome assessment are relative PPD values, attachment level, relative gingival margin level (RGML), recession depth (RD), WKG, and GT value noted with an UNC-15 probe. An acrylic cast will be made for the patient to obtain clinical parameters. An acrylic stent will be used  to cover the occlusal regions of the test tooth. By directing it using burs, the periodontal probe extends into the deepest defect site. The stent, which will act as a guide for the periodontal probe, will develop longitudinal patterns. Under local anesthesia, the GT will be measured 3 mm below using a rubber stopper and endodontic reamer to assist the gingival edge. From the cementoenamel junction to the gingival margin, RD will be evaluated. WKG will be reached by calculation of sulcus depth and attached gingiva with the UNC-15 probe. These treated areas will be measured clinically on the day of surgery and after 3 and 6 months.

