### Statistical Analysis

Both univariate and multivariate analyses will be performed to evaluate the effect of various variables (such as baseline GT, WKG, and recession length and width) on the final outcomes. Means and SDs will be calculated using standard statistical procedures to ensure significance.

The data will be analyzed as follows:

Changes from baseline to 3 and 6 months will be assessed using a Student paired *t* test.Comparisons between treatment groups at baseline, 3 months, and 6 months will be conducted using a Student unpaired *t* test.

In addition to these tests, multivariate analyses, such as multiple regression and analysis of covariance, will be used to determine the combined effects of covariates like baseline GT, WKG, and recession dimensions on treatment outcomes. These methods will allow for the assessment of potential interactions and the adjustment of confounding variables. The threshold for statistical significance will be set at *P*<.05.

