## Results

The combination of the M-VISTA technique with T-PRF is expected to significantly enhance the efficiency and effectiveness of root coverage procedures. This approach is projected to deliver superior outcomes across key clinical parameters, including reductions in PPD and RD and improvements in CAL, relative attachment level, and RGML, as well as notable increases in the thickness of attached gingiva.

This study was initiated in July 2024 with a 3-month phase dedicated to recruitment, participant selection, baseline data collection, and randomization of groups, which concluded in September 2024. The intervention phase, which is currently underway (October 2024 to December 2025), focuses on performing T-PRF and CTG procedures for both groups using the M-VISTA technique. From January 2025 to June 2026, the follow-up phase will be conducted, involving monthly clinical assessments and monitoring of clinical parameters. Finally, the study will conclude in June 2026 with a 2-month phase for final evaluations, data analysis, comparison of results, and preparation for publication. This structured timeline ensures a systematic approach to achieving the study objectives. The study timeline is outlined in Table 2.

**Table 2 table2:** Study timeline table.

Timeline	Study procedures	Duration
July 2024-Sept 2024	Recruitment, participant selection, baseline data collection, and randomization of groups	3 months
Oct 2024-Dec 2025	Intervention phase: T-PRF^a^ and CTG^b^ procedures for both groups using M-VISTA^c^ technique	15 months
Jan 2025-June 2026	Follow-up phase: monthly clinical assessments and monitoring of clinical parameters	18 months
June 2026-July 2026	Final evaluation, data analysis, comparison of results, conclusion of study, publication preparation	2 months

^a^T-PRF: titanium-prepared platelet-rich fibrin.

^b^CTG: connective tissue graft.

^c^M-VISTA: modified vestibular incision supraperiosteal tunnel access.

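### If RGML and relative attachment level are read from the patient's stent, comparing their raw values between arms wastes precision; compare them on their own baseline and treat them as checks on RD and CAL

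*Protocol article*

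**What the plan says.** Under Clinical parameters the article lists the outcomes: "Clinical parameters measured for outcome assessment are relative PPD values, attachment level, relative gingival margin level (RGML), recession depth (RD), WKG, and GT". It describes an individual device ("An acrylic cast will be made for the patient to obtain clinical parameters") and an acrylic stent over the occlusal part of the tooth. The stent's stated role is to guide the probe: "The stent, which will act as a guide for the periodontal probe, will develop longitudinal patterns". Only RD has a stated reference: "From the cementoenamel junction to the gingival margin, RD will be evaluated".

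The Results section, which sets out expected findings, names attachment on two scales and places both beside the margin measures: "including reductions in PPD and RD and improvements in CAL, relative attachment level, and RGML". The abbreviation list defines RAL as relative attachment level.

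The Statistical Analysis section says: "Comparisons between treatment groups at baseline, 3 months, and 6 months will be conducted", by unpaired t test. Change from baseline is tested by paired t test, which the Methods paragraph of the Abstract places within each group. Regression and ANCOVA are also planned; the covariates given as examples are baseline GT, WKG and recession dimensions. No between-arm test of change is named, and neither is adjustment for the baseline value of RGML or attachment level.

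**The concern.** A distance read from a custom stent has no zero shared between patients. It equals the anatomical distance plus the gap from stent to CEJ on that tooth. Teeth in either jaw may be treated (Methods, Overview), so the gap will vary. Subtracting the same site's baseline removes it; comparing follow-up values between arms does not. For the two relative outcomes, the planned unpaired tests would then carry variation from stents and crown heights on top of variation in recession, and the baseline test would say little about whether the arms began with similar recession.

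There is also overlap. If stent and CEJ are both fixed and the site is the same, a change in RGML is a change in RD, and a change in relative attachment level is a change in CAL. Agreement between the members of each pair would confirm the measurement but would not add evidence of efficacy.

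**Working it through.** **Model.** Let c be the stent-to-CEJ distance at a site, fixed over time. If the stent is the zero:

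- RGML = c + RD
- RAL = c + RD + PPD = c + CAL

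Subtracting baseline cancels c, so change in RGML = change in RD, and change in RAL = change in RD + change in PPD = change in CAL, up to measurement error. A follow-up value keeps c, so its variance is the variance of RD (or CAL) plus the variance of c, taking the two as independent.

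**Inputs.**

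- From Sample Size Calculation: SD = (1.32 + 1.10)/2 = 1.21 mm, D = 1.07 mm, two-sided 0.05 (Z = 1.96), Z = 0.84 for 80% power, 12 per group.
- Assumed, because the documents give no figure: between-patient SD of the offset, s = 1.0, 1.5 or 2.0 mm, with one offset per patient.
- Assumed: correlation of 0.5 between baseline and follow-up on the CEJ scale.

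**The plan's own figure.** The article gives no figure for RGML or attachment level. The usual two-means formula with its inputs gives 2 × (2.80 × 1.21/1.07)² = 20.05, or 21 per group, and not the stated 12. That is a separate matter, but it explains why the starting power below is about 54% and not 80%.

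**Raw comparison at 12 per group.** Total SD = √(1.21² + s²); SE of the difference = total SD × √(2/12); power from the noncentral t distribution with 22 df.

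| s (mm, assumed) | Total SD | SE of difference | Power |
|---|---|---|---|
| 0 | 1.21 | 0.494 | 0.54 |
| 1.0 | 1.57 | 0.641 | 0.36 |
| 1.5 | 1.93 | 0.787 | 0.26 |
| 2.0 | 2.34 | 0.954 | 0.19 |

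**Baseline comparison.** The offset alone gives a between-arm difference with SE s√(2/12), which is 0.41 mm at s = 1 and 0.82 mm at s = 2. A chance gap above 0.5 mm from this source would occur in 22% and 54% of trials respectively.

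**Bias and type I error.** In 20,000 simulated trials with s = 2 mm, the mean raw RGML difference was -1.06 mm against a true -1.07 mm, and the type I error was 0.049. Power was 0.18 for raw RGML and 0.54 for raw RD. Change in RGML and change in RD agreed in every simulated patient, each with power 0.54.

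**Would the named covariates help?** Adjusting for baseline RD leaves c in place. The residual SD is √(1.21² × 0.75 + s²): 1.45, 1.83 and 2.26 mm for s = 1.0, 1.5 and 2.0, with power 0.41, 0.28 and 0.20 (21 df).

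**ANCOVA on own baseline.** The correlation of raw values is ρ = (s² + 0.5 × 1.21²)/(s² + 1.21²) = 0.70, 0.80 and 0.87. The residual SD is total SD × √(1 − ρ²) = 1.12, 1.15 and 1.17 mm, with power 0.61, 0.59 and 0.57. Simulation that also estimates the slope gives slightly less: 0.59, 0.56 and 0.55.

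**The case against.** The strongest objection is that the stent zero is inferred. The article calls the stent a guide for the probe and states no zero, and its Clinical parameters section says only attachment level; the word relative is attached to it in the Results section and the abbreviation list. This stands, and the point is conditional on it. The inference is still a good one: a relative margin level listed apart from CEJ-referenced RD needs another reference, and the stent is the only other fixed one described.

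Second, a reader might infer that chance differences between stents could create a false treatment effect. They do not. The t test's standard error already includes the offset variance, as the simulated type I error shows. RD and CEJ-based CAL also keep their information, so a weak RGML test does not cost the trial its answer on recession.

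Third, a reader might infer that the plan counts two measurements as five independent successes. The Results section lists the parameters side by side in a sentence of expectations; it does not call them independent or set a rule for counting them. The equalities themselves need the same site, axis and zero, and the article does not say that RD is read at the stent-guided site.

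Fourth, the offset SD is assumed, and 1.21 and 1.07 mm were set for measurements such as PPD and CAL, not RGML. Averaging several teeth per patient would shrink the part of the offset that varies between teeth. The power figures therefore illustrate the effect and do not predict it.

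Fifth, paired change tests and ANCOVA are already planned, with an open list of covariates. But the change tests are within arm, and the named covariates do not contain the offset. Finally, the absence of a stated CEJ-referenced CAL reading could be taken as a flaw; an article may leave that detail to the full protocol, so it is not held against the plan.

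**Conclusion.** The point holds as a matter of precision and presentation for two outcomes, RGML and relative attachment level, on the condition that they are read from the stent. With an assumed offset SD of 1 to 2 mm, power of the planned raw comparison at 12 per group would fall from about 54% to 36–19%, and the baseline comparison of these outcomes would say little about recession severity. The documents do not support a claim of bias, of inflated type I error, or of harm to the RD or CEJ-based CAL comparisons. If the zero were instead the CEJ, the loss of precision would disappear, but RGML would simply be RD and the overlap would be complete. The change is worth making because it uses readings already planned.

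**What to change.** - State the reference point for RGML and for attachment level.
- If it is the stent, compare these two outcomes between arms at 3 and 6 months by ANCOVA on their own baseline value, or as same-site change from baseline.
- Drop their raw group comparisons at baseline, 3 and 6 months.
- Present change in RGML against change in RD, and change in relative attachment level against change in CAL, as measurement checks and not as additional efficacy results.

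This changes analysis wording only; the readings are already scheduled for the day of surgery, 3 and 6 months. The downside is fewer separately claimed outcomes.
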